### Interventions

Both intervention protocols are based on the Movement Assessment Battery for Children – Second edition (MABC-2) domains: Manual Dexterity, Aiming and Catching, and Balance. Six games/activities for Nintendo Wii are used that target these domains and six no-Wii activities that are compatible with the activities selected for Wii. The reason for selecting these six of activities is that they address potential improvements in the skills that are required for the standard assessment for children with DCD. The second reason was to render the games/activities as close as possible to those required for MABC-2 evaluation in terms of movement standard.

Each game/activity will continue for 7 min and in total 42 min will be spent on the six activities. With the purpose of exchanging materials and equipment from one game to the next, thus allowing to complete the total time of 60 min per session.

Sessions of both protocols will be performed twice a week, with duration of 60 min per session, and with a minimum of 12, and a maximum of 16 training sessions in total. The first session will familiarize the children with the games/activities. The second sessions consists of a pre-test and the last the post-test for motor learning outcome. The number of mistakes, hits, and respective score will be counted in each one of the games/activities. Pre-post scores for each training condition will be compared. The two protocols each have six activities. For the protocol with Wii, existing games will be use and for the no-Wii protocol ‘real life’ activities will be used that target the same domains as the Wii tasks.

The total score for each session will be the sum of the points obtained in all the attempts performed. The sequence of the games will be randomized, with a selection among 16 possible combinations, considering two activities for the same domain in sequence in all of these combinations (Tables 1, 2 and 3).

**Table 1 Tab1:** Intervention protocol sequence of activities

Session number	Activity 1	Activity 2	Activity 3	Activity 4	Activity 5	Activity 6
1	Bow and arrow/archery	Bowling	Frisbee	Table tennis	Balance disk/marble balance	Balance beams/tightrope walk
2	Bow and arrow/archery	Bowling	Balance disk/marble balance	Balance beams/tightrope walk	Frisbee	Table tennis
3	Table tennis	Frisbee	Bowling	Bow and arrow/archery	Balance disk/marble balance	Balance beams/tightrope walk
4	Balance beams/tightrope walk	Balance disk/marble balance	Table tennis	Frisbee	Bow and arrow/archery	Bowling
5	Balance disk/marble balance	Balance beams/tightrope walk	Frisbee	Table tennis	Bowling	Bow and arrow/archery
6	Table tennis	Frisbee	Bow and arrow/archery	Bowling	Balance beams/tightrope walk	Balance disk/marble balance
7	Bow and arrow/archery	Bowling	Balance beams/tightrope walk	Balance disk/marble balance	Table tennis	Frisbee
8	Bow and arrow/archery	Bowling	Table tennis	Frisbee	Balance disk/marble balance	Balance beams/tightrope walk
9	Balance beams/tightrope walk	Balance disk/marble balance	Frisbee	Table tennis	Bowling	Bow and arrow/archery
10	Frisbee	Table tennis	Bow and arrow/archery	Bowling	Balance disk/marble balance	Balance beams/tightrope walk
11	Balance beams/tightrope walk	Balance disk/marble balance	Bow and arrow/archery	Bowling	Table tennis	Frisbee
12	Bowling	Bow and arrow/archery	Frisbee	Table tennis	Balance disk/marble balance	Balance beams/tightrope walk
13	Balance beams/tightrope walk	Balance disk/marble balance	Bowling	Bow and arrow/archery	Frisbee	Table tennis
14	Balance disk/marble balance	Balance beams/tightrope walk	Bowling	Bow and arrow/archery	Frisbee	Table tennis
15	Bowling	Bow and arrow/archery	Balance disk/marble balance	Balance beams/tightrope walk	Frisbee	Table tennis
16	Frisbee	Table tennis	Bowling	Bow and arrow/archery	Balance disk/marble balance	Balance beams/tightrope walk

**Table 2 Tab2:** Training activities with Wii and the three domains

Manual Dexterity	Aiming and Catching	Balance
Frisbee	Bowling	Tightrope walk
Table tennis	Archery	Marble balance

**Table 3 Tab3:** No-Wii Experimental protocol activities

Manual Dexterity	Aiming and Catching	Balance
Frisbee	Bowling	Balance disk
Table tennis	Bow and arrow	Balance beams

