### Secondary outcomes measures

#### Motor learning

Motor learning in children will be assessed by means of the score obtained in the games. Individual scores in each of the six games from the second session (pre-test) will be summated as well as those from the six games of the last session (post-test) to obtain the general measurement of motor learning due to the treatment.

Individual scores in each game and for domain will also be counted (Manual Dexterity, Aiming and Catching, and Balance), before and after intervention. With the purpose of analyzing whether some activities are better learned in one type of intervention than in another. A specific form will be available for each therapist fills this information in each session.

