### Sample size

Sample size was calculated using the G*Power Software (3.1.9.2 version, Germany) based on a pilot study (*n* = 6). The calculation was performed considering the within-group comparisons for the Wii group, a power of 80%, and an alpha of 5%. The MABC total score assessed before and after 12 sessions was considered the main outcome and then considered for the analysis. The effect size was 0.80 (baseline: 58.0 ± 8.7; post 12-session intervention: 65.5 ± 9.9). Therefore, a sample of 15 participants was required for each group. In order to account for possible dropouts, we increased the sample to 16.

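### The motor-learning post-test falls at each child's last session (12th to 16th) and never in the pre-test activity order, so gains mix learning with unequal practice and position

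*Protocol article*

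**What the plan says.** In the protocol article, Interventions sets the course at two sessions a week, "with a minimum of 12, and a maximum of 16 training sessions in total"; the Abstract makes clear that this range applies per child. On the role of particular sessions: "The first session will familiarize the children with the games/activities", and then "The second sessions consists of a pre-test and the last the post-test for motor learning outcome". The Motor learning section, under the secondary outcomes, repeats the rule. The six game scores from session 2 are summed and set against the six from the last session, and scores by game and by domain are also compared to see whether some activities are learned better in one program.

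On order, Interventions states "The sequence of the games will be randomized, with a selection among 16 possible combinations". Table 1, titled "Intervention protocol sequence of activities", lists one order for each session number from 1 to 16, and each cell pairs the Wii activity with its no-Wii counterpart.

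On recording, the Motor learning section states "A specific form will be available for each therapist fills this information in each session". On planning, Sample size states "The MABC total score assessed before and after 12 sessions was considered the main outcome".

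The text shown does not say how a child's session count between 12 and 16 is decided. It sets no common post-test session and no common order for the two test sessions.

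**The concern.** A score earned by playing the trained games depends directly on how much the child has practised them. If one child is tested at the 12th session and another at the 16th, two children with the same learning rate will show different gains. Session count also arises after randomisation: families may stop at any time (Ethical approval), so it cannot be treated as a baseline characteristic.

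Activity order adds a second component. A game played first in one session and fifth in another is exposed to different warm-up and fatigue. If its place changes between the two tests, the change in score includes that effect as well as learning. The per-game and per-domain comparisons are the most exposed, because each activity moves by a different amount and the amount depends on which session happens to be last.

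Motor learning is formally secondary, but the Abstract and Background describe the trial's purpose as comparing the programs on motor learning, so a clean definition matters.

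**Working it through.** **Inputs.** Pre-test at session 2; post-test at session L, with L from 12 to 16; two sessions a week (all Interventions). Time per activity: "Each game/activity will continue for 7 min and in total 42 min will be spent on the six activities"; this agrees with its parts, 6 × 7 = 42 min. Activity orders are from Table 1. The protocol gives no numerical target for motor learning. Its sample size rests on the MABC total score, so it plays no part here.

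**Practice between the tests.** Session 1 precedes the pre-test and does not count.
- Sessions strictly between the tests = L − 3: 12 − 3 = 9 and 16 − 3 = 13.
- Practice per activity = 7 × (L − 3): 7 × 9 = 63 min and 7 × 13 = 91 min.
- Ratio = 13 / 9 = 1.44, so 44% more practice at the extreme.
- Counting the post-test session itself gives 10 to 14 sessions and 14 / 10 = 1.40; the conclusion is the same.
- Time from pre-test to post-test = (L − 2) / 2 weeks: (12 − 2) / 2 = 5 and (16 − 2) / 2 = 7. The whole course is 12 / 2 = 6 to 16 / 2 = 8 weeks, which is a different interval.

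**Order under Table 1.** Key: A = archery/bow and arrow, W = bowling, F = frisbee, T = table tennis, D = balance disk/marble balance, B = balance beams/tightrope walk. Session 2 runs A W D B F T.

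| Last session | Order | Activities whose position changes from session 2 | Sessions strictly between | Min per activity |
|---|---|---|---|---|
| 12 | W A F T D B | 6 | 9 | 63 |
| 13 | B D W A F T | 4 | 10 | 70 |
| 14 | D B W A F T | 4 | 11 | 77 |
| 15 | W A D B F T | 2 (A and W swap) | 12 | 84 |
| 16 | F T W A D B | 6 | 13 | 91 |

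All 16 rows of Table 1 are distinct, so no possible last session repeats the session-2 order. Frisbee, for example, is 5th at the pre-test (after 4 × 7 = 28 min of play), 3rd at session 12 (after 2 × 7 = 14 min), 5th at sessions 13 to 15, and 1st at session 16 (0 min).

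**If the order is drawn rather than fixed by row.** The text on random selection and the numbered rows do not settle which applies. If one of the 16 orders is drawn independently each session, the two test orders match with probability 1/16. The mismatch remains, but as noise rather than a shift tied to session number.

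**The case against.** The case on the other side has real force on several points.

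- **A reader might infer that the comparison between Wii and no-Wii is biased.** The documents do not show this. Both arms have the same session range, and each row of Table 1 serves both, so common practice and order effects largely cancel. Bias needs session counts, or the effects themselves, to differ by arm. The Discussion expects the Wii to be motivating, but nowhere ties motivation to the number of sessions. A difference is possible, not shown.
- **A reader might infer that the primary outcome is undermined.** Game order does not enter the MABC-2 score, and the concern is about a secondary outcome. The MABC-2 and DCDQ are planned before and after the intervention. Moving them to a fixed date would be a debatable trade-off: it would fall before some children finish, or well after others have. That is not part of this point.
- **A reader might see the 12-session planning basis as contradicting the 12-to-16 range.** Twelve is the stated minimum, so the two are compatible; they are simply not reconciled.
- **The order change is uneven.** Both Manual Dexterity games keep their pre-test places at sessions 13 to 15, and session 15 only swaps archery and bowling. The shift of frisbee from 28 min to 0 min is the most extreme of five cases.
- **A rule for session count may exist elsewhere**, in the full protocol or in Fig. 8, neither of which is shown. That is fair, and absence of such a rule is not the point. A rule for who stops when would still leave the post-test at different sessions for different children, because the article itself places it at the last one.

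What remains is the stated measurement rule. It ties the score to unequal practice, and under Table 1 it always pairs two different orders.

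**Conclusion.** The concern holds for the secondary motor-learning outcome. As defined, the pre-post gain combines learning with practice that ranges from 9 to 13 intervening sessions (63 to 91 min per activity, up to 44% more) and, under Table 1, with a position change affecting two to six of the six activities. Within-arm gains and the per-game and per-domain results are confounded with both.

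For the between-arm comparison the established consequence is limited to added noise, with bias only if session counts, or practice or order effects, differ by arm. The documents give no per-session practice effect, no order effect and no distribution of session counts, so the size of any distortion in scores cannot be estimated.

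The practice figures assume that children complete between 12 and 16 sessions as stated. The position counts assume that the rows of Table 1 apply by session number.

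**What to change.** Leave the number of sessions each child receives as it is, and change only what is scored:

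1. Define the motor-learning post-test as the session-12 score for every child, for the total, by game and by domain. Every child who completes the minimum course reaches session 12, and scores are already recorded at each session, so no new data are needed. All children then have 9 sessions between the tests.
2. Use the session-2 activity order at session 12, and state that Table 1 applies by session number at these two test sessions. Because all 16 rows are distinct, the session-12 row must be replaced; exchanging two rows would not produce a match.
3. Report scores from sessions 13 to 16 descriptively, as a continuation of the learning curve.
4. In Sample size, reconcile the 12-session planning basis with the 12-to-16 range. No change to the timing of the MABC-2 or DCDQ is asked for.

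The cost is wording and one replaced row. Practice after session 12 no longer enters the motor-learning summary, and one of the 16 listed orders is lost, so the stated count of 16 combinations needs correcting to 15. The order change has to be made before the test sessions take place, because matched-order scores cannot be recovered in the analysis.

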### Experimental protocol with Wii

This protocol was based on percepto-motor activities, consisting of activities and games based on VR, supported by Nintendo® Wii resources: the Wiimote control and the WBB platform, communicating via bluetooth. The training activities are detailed below:

### Frisbee

This activity will be performed with the children holding the Wiimote control in the fist, in a space of 1.10 m^2^, at a 2-m distance from the television screen to which the Nintendo® Wii will be connected, performing throws of the virtual Frisbee, aiming to hit the target in the scoring area projected.

Children will be encouraged to perform the highest number possible of throws in the period of 7 min, trying to hit the scoring areas worth 10, 50, and 100 points. Every time the Frisbee hits these spaces, it will count as a hit and as a mistake each time it hits outside them. The sum of all attempts hitting any scoring area during 7 min in each session will be the basis of the score.

### Table tennis

This activity will be performed with the children holding the Wiimote remote control in their fist, and they will be encouraged to use it as if it were a table tennis paddle, to serve, hit and hit the ball again, trying to score more points than the opponent (virtual opponent chosen by the machine). Each game will automatically end when one of the players scores 8 points. Each point scored by the children will count as a hit and those scored by the opponent (machine) as a mistake. The children must score the maximum number of points in 7 min.

### Bowling

This activity will be performed with the Wiimote control held in the fist, which serves as if it were the bowling ball. The aim is to perform the throws and try to knock down the highest number of pins. Two blocks of nine attempts will be performed. At the end of the 10th block, children will start a new session of two attempts each until the end of the 7-min period. Each throw knocking pins down will count as a hit, or as a mistake in the opposite case. Children who knock down all 10 pins at once will be considered Strikers and will double the score for the next throw, while those knocking down the 10 pins in two throws (first to ninth blocks) or three (10th block) will be considered a Semi-Striker, receiving half of the score they achieve in the next throw as a surplus.

### Archery

This activity will be performed with the Wiimote remote control held in the children’s fist. The movement to be performed with the Wiimote should represent the action of a bow moving the arrow to reach the aim with different scoring areas, varying from 1 to 10 points. The children, in the figure of an avatar, will go through three stages of the game at the beginner level, each one with different scenery and distances (10 m, 25 m, and 35 m) between avatar and aim.

At the end of the three stages of attempts, children will return to the beginning stage and continue to perform new attempts until the end of the 7-min period. Each arrow shot and sticking to the target will count as a hit, and as a mistake in the opposite case. The total score for each session will be the sum of the points obtained in all the attempts performed.

### Tightrope walk

This activity will be performed with the WBB equipment, fixed to the ground, in a space of 1.10 m^2^ and at a distance of 2 m from the television screen. Children will have to step with both feet on the equipment and perform the action of the game, consisting in a 35-m tightrope walk between the top of virtual buildings. As a form of equalizing scores, the total length of the rope is divided in three parts: the two first of 12 m each and the last of 11.

The basic movement that children will perform is raising their feet alternately, moving the trunk sideward so that the avatar maintains the balance as it walks on the rope. Each third part of the rope walked without falling will count as a hit, while any fall in lengths shorter than 12 or 11 m will count as a mistake. The first 12 m walked will be worth 15 points, the 12 intermediary meters will be worth 20, and the last 11 m 10 points.

### Marble balance

This activity will be performed with the WBB equipment fixed to the ground, similar to what described for the tightrope walk. Children will move their trunk to different positions while trying to throw the ball in the holes of the virtual platform, which will be turning all the time, provoking greater unbalance and difficulty in the game. Every ball falling out of the virtual platform will count as an error, and each one in the respective hole will be worth a point. As the balls disappear, the children will move to a new platform, with more balls to be thrown into the holes. Scores will be calculated by the Nintendo® Wii equipment itself with basis on the performance of the avatar commanded by the children.

### Experimental protocol no-Wii training

This protocol was based on a proposal of percepto-motor type, and named no-Wii training. Its training protocol is detailed on the following table:

### Frisbee

The game of Frisbee consists in throwing a Styrofoam disk measuring 24 cm of circumference (Fig. 2a) on a paper card target with a circumference of 2.82 m and placed at a distance of 4 m (Fig. 2b). The target must be fixed to the ground and display three different scoring areas (10, 50, and 100 points).

**Fig. 2 Fig2:**
[figure not shown]
**a** Frisbee, **b** Frisbee target

### Table tennis

The game of table tennis will be performed with the elevation of one of the two halves of the table, allowing children to throw and hit the ball again with their paddle (Fig. 3). The aim of this activity consists in making the ball hit the raised half of the table after it hits the horizontal part and going back to the same side, and children will be given a hit for each movement of this kind. Balls falling out of the game area, multiple rebouncing on the horizontal part of the table and a serving or reception error will count as mistakes.

**Fig. 3 Fig3:**
[figure not shown]
Tennis table

### Bowling

The game of bowling will be performed with the use of 10 PET bottles containing 600 ml of water each (Fig. 4), placed at a distance of 4.83 m for children aged 7 and 8 years, and at a distance of 6.03 m for those aged 9 and 10 years. The aim of the activity is to throw a 0.5-kg medicine ball towards the bottles and knock down the highest number possible at once (Fig. 4).

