**Fig. 5 Fig5:**
[figure not shown]
**a** Bow and arrow, **b** Target for bow and arrow

A wooden target, covered with an adherent plastic surface so that the suction cups at the tip of the arrows stick to it, will be used. It measures 41 cm in circumference, and it will be fixed to the wall with a 120-cm adjustable rope in front of the children, at their visual height, at a distance of 2.30 m for 7- and 8-year-old children and 2.97 for children aged 9 and 10 years. Each arrow hitting the target and sticking to a scoring area will count as a hit, while those not fixing to it as a mistake. Scores will be based on the scale displayed on the target itself, ranging from 1 to 10 points.

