### Balance disk

This activity will be performed with a vinyl balance disk measuring 40 cm in circumference (Fig. 6) placed on the ground; the children will perform 14 different static balance postures on top of it (Table 4). The postures were based on, and adapted from, the Berg Balance Scale [28]. Children aged 7 and 8 years must maintain the postures for 15 s, while 9- and 10-year-old children must keep them for 30 s. Each posture performed correctly and for the time due will count as a hit, while unbalances, falls, stepping on feet or putting hands on the ground will be regarded as mistakes. In the second case, children must go to the following posture. Each hit will be worth 10 points, and at the end of the 14 postures, they will repeat the same sequence until the time is over.

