## Discussion

This study protocol is the first to directly compare the efficacy of two motor-training protocols in children with DCD. The protocol is based on the domains of the MABC-2 domains. Various studies have already demonstrated the efficacy of intervention programs based on VR for these children [19–24, 31–36], but the absence of further protocol systematization has been an important hindrance for professionals and researchers in this field to clearly understand the impact of such interventions on children’s activity performance.

Studies comparing interventions based on VR and conventional interventions [19, 22–24] are scarce, and their results tend to demonstrate that despite the benefits of VR, conventional interventions seem to be more effective in the improvement of motor performance of children with DCD [19, 22–24]. Due to limitations and differences between the protocols adopted, though, these results must be interpreted carefully. Hence, when testing the efficacy of these two type of intervention programs, planned in similar manner, with similar scoring systems and activities, it will be possible to enhance evidence about the benefits in motor performance and learning of one program over the other.

One documented advantage of VR training, such as the Wii intervention, is the motivating aspects because the projected architecture on the environment of VR is capable of hold the children’s attention, being an important aspect for rehabilitation of children with DCD [20].

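### Three no-Wii activities become more demanding at age 9 and no Wii game is stated to, so the raw motor-learning comparison between arms depends on the age mix, which neither the draw nor the named analysis takes into account

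*Protocol article*

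**What the plan says.** All references are to the protocol article.

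- **No-Wii activities with an age rule.** Bowling: 4.83 m for ages 7 and 8, and "at a distance of 6.03 m for those aged 9 and 10 years". Bow and arrow: "2.30 m for 7- and 8-year-old children and 2.97 for children aged 9 and 10 years" (the second figure has no unit; metres are presumed). Balance disk: "Children aged 7 and 8 years must maintain the postures for 15 s, while 9- and 10-year-old children must keep them for 30 s".
- **No-Wii activities without one.** Frisbee, table tennis and balance beams.
- **Wii games.** None of the six descriptions gives an age rule. Archery, for instance, takes every child through three beginner stages, "each one with different scenery and distances (10 m, 25 m, and 35 m) between avatar and aim".
- **Scoring.** Points do not change with age. On the disk, "Each hit will be worth 10 points"; in bowling each bottle counts one point.
- **Outcome.** Under Motor learning, the six game scores are summed for session 2 and for the last session. Scores by game and by domain are to show whether activities are learned better in one arm than in the other.
- **Allocation and analysis.** The Randomization section describes a draw with a run-of-four rule and no age stratum. Statistical methods names ANOVA and ANCOVA without listing covariates, with Mann-Whitney and Wilcoxon tests as the fallback.
- **Rationale.** The Discussion bases the comparison on the two programs being "planned in similar manner, with similar scoring systems and activities".

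**The concern.** A point earned at age 10 in no-Wii bowling, bow and arrow or balance disk is not the same unit as a point earned at age 7. No corresponding step is stated on the Wii side. Age therefore enters the summed score, and the gain in it, differently in the two arms. Two things follow. First, a chance excess of older children in one arm can move the arm difference without any difference in learning. Second, even with the ages perfectly balanced, the pooled difference averages two unlike contrasts, with weights set by the age mix that happens to be recruited.

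At stake is the motor-learning comparison. It is listed as a secondary outcome, although the Abstract and Background give motor learning as the aim of the trial.

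**Working it through.** **The plan's own figure.** The plan gives no figure for this point. Its sample size matters here only as the arm size, and it reproduces: a paired t-test, two-sided 5%, d = 0.80, n = 15 has power 82.1%. That calculation concerns the MABC total score within the Wii group. The 16 after the dropout allowance is read as per arm.

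**Step 1: the age rules.**

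| No-Wii activity | Ages 7–8 | Ages 9–10 | Ratio |
|---|---|---|---|
| Bowling distance | 4.83 m | 6.03 m | 6.03/4.83 = 1.25 |
| Bow-and-arrow distance | 2.30 m | 2.97 | 2.97/2.30 = 1.29 |
| Balance disk hold | 15 s | 30 s | 30/15 = 2 |

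Three of six no-Wii activities have a rule; none of the six Wii games states one.

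**Step 2: what is mechanical.** For the disk, the ceiling follows from the text alone. The Interventions section says: "Each game/activity will continue for 7 min", that is, 420 s. With no changeover time:

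- ages 7–8: 420/15 = 28 holds × 10 = 280 points;
- ages 9–10: 420/30 = 14 holds × 10 = 140 points.

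The mean ceiling in a no-Wii arm with 25%, 50% or 75% aged 9–10 is 245, 210 or 175 points (for example 0.75 × 280 + 0.25 × 140 = 245). If every child improves by the same 20 percentage points of the ceiling (assumption), the mean gain is 49, 42 or 35 points. For bowling and for bow and arrow, the article gives nothing from which a size can be computed.

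**Step 3: how often the arms differ in age.** Assume half the children are 9–10.

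- Two independent Bin(16, 0.5) counts differ by 4 or more with probability 0.215, about 22%.
- Simulating the draw with its run-of-four rule (16 of 32 children aged 9–10) gives 22% for a gap of at least 25 percentage points in the share aged 9–10.
- Fixing 16 per arm and varying the number aged 9–10 from 8 to 20 of 32 (hypergeometric) gives 22% to 29%.

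**Step 4: what such a gap does to the no-Wii mean gain.** Assume the gain on an age-scaled task is 1 at ages 7–8 and 0.5 at ages 9–10. Take a 4-child gap as 6 versus 10 older children of 16.

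- *Single age-scaled game.* 6 older: (10 × 1 + 6 × 0.5)/16 = 0.8125. 10 older: (6 × 1 + 10 × 0.5)/16 = 0.6875. Ratio 0.846, so 15% lower. Measured from the expected 8 older children, (8 × 1 + 8 × 0.5)/16 = 0.75, it is 0.6875/0.75 = 0.917, so 8% lower.
- *Summed score.* Suppose the three age-scaled tasks supply half of a younger child's gain (assumption). Then 0.5 + 0.5 × 0.8125 = 0.906 versus 0.5 + 0.5 × 0.6875 = 0.844. Ratio 0.931, so 7% lower.

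**The case against.** - **Randomization balances age on average, so a chance gap is sampling error and not bias.** This stands. It does not answer the second part of the concern: with equal age mixes, the raw contrast still depends on which ages were recruited.
- **The direction is unknown.** More demanding settings may offset older children's greater ability and make no-Wii scores less dependent on age. This stands for bowling and for bow and arrow. For the disk, the ceiling halves whatever the child's ability, although the effect on actual gains remains an assumption.
- **The summed effect may be below 7%.** Frisbee, which has no age rule, pays 10, 50 or 100 points a hit, against 1 per bottle and 1 to 10 per arrow. The age-scaled tasks may therefore supply less than half of the gain. This stands; the game and domain results are more exposed than the sum.
- **An unseen analysis plan may list age as a covariate.** It may. A reader might infer that no age adjustment is intended, but the text supports only that none is named. Age as a main effect alone would still leave the age effect that differs by arm.
- **The Wii games may not be constant across ages.** The article is silent on age there, and silence does not prove constancy: the table tennis opponent is chosen by the machine, and marble balance moves to platforms with more balls. What stands is that no age rule is stated.
- **Raw points differ between paired tasks at every age.** The disk pays 10 per posture and marble balance 1 per ball. This is correct, and it means that handling age alone would not put the arms on a common scale.

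**Conclusion.** The point holds as a modest, cheaply corrected weakness in a secondary outcome. The age rules apply on one side only, points are not rescaled, and the disk maximum falls from 280 to 140 points at age 9. On the stated assumptions (half the children aged 9–10, 16 per arm, gains halved from age 9 on the age-scaled tasks), a gap of four or more older children arises in about 22% of trials. A 6-versus-10 gap then moves the no-Wii mean gain by about 7% on the summed score, or up to 15% on one age-scaled game.

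Two stronger readings are not supported:

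- A reader might infer a shift near 29%, by setting a no-Wii arm with 4 older children against one with 12 (0.875 versus 0.625). Those counts are tail events, 3.8% each under Bin(16, 0.5), and the figure needs the halving to hold for all six activities when only three have an age rule.
- A reader might infer that the trial's main result is affected. The primary outcome, the MABC-2 total standard score, is not built from game points. Difficulty is also fixed within a child unless a ninth birthday falls during training, so the direction of within-child change is preserved and only the scale of the gain is in question.

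No view is taken on which distance or hold time is right.

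**What to change.** 1. **Draw.** Draw separately within ages 7–8 and 9–10, since age is known beforehand. Keep each list balanced in itself, for example with permuted blocks: two lists of unrestricted draws would balance age no better than one.
2. **Scale.** Before summing and comparing arms, express each game score relative to its activity and age band, either standardised to the session-2 mean and SD or as the proportion of hits. Hits and mistakes are already counted. This also deals with the unlike point scales of the paired tasks.
3. **Model.** Include age band at allocation and arm × age band. Report the arm difference averaged over the age bands, with the per-band differences as descriptive only.
4. **Fallback.** A plain Mann-Whitney test cannot take these terms, so apply it to the rescaled scores or use a rank test stratified by age band.

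Cost: two draw lists and about 2 of 30 residual degrees of freedom (32 children less two arm means). No extra children are needed and no activity changes. Per-band estimates rest on about 8 versus 8 children, with a standard error about √2 = 1.4 times that of the full comparison. Session-2 means and SDs from groups that small are themselves noisy.
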